##### Sample size calculation

This proposed pilot study is a phase II intervention study and the first of its kind in the field of neurological rehabilitation comparing two MI intervention techniques. Both intervention techniques were tested separately in randomised controlled trials with stroke patients or athletes. As the hypothesis of this investigation has not been addressed before, an a priori sample size cannot be estimated.

##### Group comparison

Group equality will be determined at baseline regarding all descriptive variables: age, gender, disease, affected brain hemisphere, time since stroke onset, cognitive function, handedness, rehabilitation history, patient's sports history, and patient's history of falls since stroke onset (over the last six to twelve months). Parametric and nonparametric tests will be used depending on statistical data level and data distribution. Furthermore, inter-group comparisons between BL and T0, T0 and T1, as well as T1 and FU will be calculated to analyse changes among all three groups over time. Additionally, intra-group comparisons for each measurement event (pre- and post-intervention; T0 vs. T1 vs. FU) will be calculated for all three groups; means, standard deviations and confidence intervals, will be given where feasible. An intention to treat analysis will be performed for drop outs. Missing values will be replaced by the average trend of all participants of the respective group.

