##### Primary outcome measure

The primary study outcome has been defined as changes in time needed to perform the motor task due to the study intervention. This primary outcome will be assessed by the difference between measurement points T0 and T1. For performance and validity reasons all assessment sessions will be videotaped. Time needed to perform the task in seconds will be derived from the video recordings.

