#### Statistical analyses

All necessary statistical analyses will be performed with the Statistical Package for the Social Sciences (SPSS) version 16. The significance level will be set at p ≤ 0.05. For all outcome measures the final analysis method will be determined after data collection tests of normal distribution and homogeneity of variances. Before data analyses collected patient data will be anonymised.

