#### Presentation of results

The patient recruitment process, the total number of included and excluded patients, as well as the dropout rate will be summarised in a CONSORT flow diagram [84]. All data describing the study population (general profile) will be presented in an overview table. The changes between assessment events and differences between study groups will be displayed in graphs and tables. Significant changes will be marked. Standard deviations and confidence intervals will be used to describe dispersion characteristics.

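### Filling missing values with the patient's own group average trend understates standard errors by about the missing fraction and inflates the false-positive rate

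*Protocol article*

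**What the plan says.** The Group comparison section of the protocol article fixes two things about incomplete data: "An intention to treat analysis will be performed for drop outs", and "Missing values will be replaced by the average trend of all participants of the respective group". The article mentions no multiple imputation, added residual variation, variance correction, likelihood-based model or sensitivity analysis.

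The rule acts on a change score. For the primary endpoint, "This primary outcome will be assessed by the difference between measurement points T0 and T1". For the group analyses, "inter-group comparisons between BL and T0, T0 and T1, as well as T1 and FU will be calculated to analyse changes among all three groups". On testing, "The significance level will be set at p ≤ 0.05", and "Parametric and nonparametric tests will be used depending on statistical data level and data distribution".

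Neither quantity that determines the size of the problem is given. On sample size the article says that "an a priori sample size cannot be estimated". Dropout appears only as a result to be reported.

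**The concern.** The rule is a deterministic single imputation, computed from the other patients in the same arm. If a patient's missing T1 time is built as the T0 time plus the arm's average trend, that patient's change equals the arm mean exactly. The arm mean does not move, the spread around it shrinks, and n and the degrees of freedom are those of a complete trial. Tests and intervals then treat the filled-in patients as independent evidence.

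The consequence runs in an awkward direction: the more data are lost, the more precise and the more significant the comparison of embedded with added motor imagery appears. The rule also credits each patient who is lost with the average improvement of the completers in that arm, and the intention-to-treat label conceals this. Intervals carried forward from this pilot into a later trial would be too narrow as well.

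**Working it through.** **Inputs from the article.** Primary endpoint: T0 to T1 change (Primary outcome measure). Level 0.05 (Statistical analyses); sidedness is not stated, so two-sided is assumed. Three groups. The plan has no figure of its own to reproduce.

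**Assumptions.** Missing fraction d from 5% to 30%, equal across arms and completely at random; normal change scores; no true effect; n from 10 to 100 per group.

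**Standard error.** Let m of n patients per arm be observed, with standard deviation s.

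- True SE of the arm mean, which rests on m patients: s/√m.
- Variance after fill-in: (m−1)s²/(n−1), so the calculated SE is √[(m−1)s²/((n−1)n)].
- Ratio of calculated to true SE: √[m(m−1)/(n(n−1))], which is about m/n = 1−d.

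Example: n = 20, m = 16 gives √(240/380) = 0.795, an understatement of about 20%, which is the missing fraction.

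**False-positive rate.** Two arms: 2[1 − Φ(1.96(1−d))]. Three groups: P(χ²₂ > 5.99(1−d)²), which equals 0.05 raised to the power (1−d)². At d = 0.20 the first is 2[1 − Φ(1.568)] = 0.117 and the second is 0.05^0.64 = 0.147.

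| Missing | SE ratio | Two-arm | Three-group | Correct interval wider by 1/(1−d) − 1 |
|---|---|---|---|---|
| 5% | 0.95 | 6.3% | 6.7% | 5% |
| 10% | 0.90 | 7.8% | 8.8% | 11% |
| 20% | 0.80 | 11.7% | 14.7% | 25% |
| 30% | 0.70 | 17.0% | 23.0% | 43% |

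At 20% missing, a nominal 95% interval for the two-arm difference covers about 100 − 11.7 = 88%.

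**Simulation check.** There were 40,000 null trials per setting, counting only group sizes at which the missing fraction is a whole number of patients.

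- 10% missing: two-arm t-test 7.6% to 8.1%, three-group ANOVA 8.5% to 9.0%.
- 20% missing: 11.7% to 12.1% and 14.6% to 15.0%.
- 30% missing: 16.9% to 17.6% and 22.8% to 23.3%.

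The result hardly depends on n. Letting the number of dropouts vary at random around 20% gives 12.1% to 12.6% for two arms.

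**Other planned tests at 20% missing.** The within-group pre-post test gives about 11.5% to 11.9%. The nonparametric route is no refuge: Mann-Whitney (3,000 trials per setting) gives 12.5% at n = 10 and 24% at n = 100, because the filled-in values are tied at the arm mean.

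**Without the fill-in.** With 20% missing, observed change scores alone give 4.9% to 5.1%.

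**The case against.** Several points on the other side have force.

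- **The dropout rate is unknown and could be low.** Allocation follows T0, and the primary window is a two-week course of six sessions. Only losses in that window affect the primary contrast. At 5% missing the inflation is modest, and with complete data there is none. A reader might infer that this trial's false-positive rate is doubled. The article does not support that, because about 12% belongs to an assumed 20% missing.
- **The average trend is not defined.** Setting the change to the arm mean is the natural reading for a change score, but it is an inference. If raw T1 times were compared instead, the rate at 20% missing would be only about 6.7%, assuming a T0–T1 correlation of 0.7. The article, however, defines the outcome as the change.
- **Not every comparison suffers.** BL and T0 both precede randomisation, so dropout after allocation cannot affect that contrast. The problem concerns T0 to T1 and T1 to FU.
- **It is a pilot.** The article describes a phase II pilot and will report dropout: "as well as the dropout rate will be summarised in a CONSORT flow diagram". It nevertheless tests at 0.05, plans to mark significant changes, and says in its abstract that the results will determine whether embedded imagery is superior.

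A reader might also infer that the rule biases the comparison towards one arm. Under random missingness it does not: the filled-in arm mean equals the completers' mean, and only the precision is false. Bias would need informative dropout, which the article gives no means of quantifying. Nor does it say that a patient unable to perform the task has a missing time, so it cannot be claimed that such patients would be credited with an average improvement.

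**Conclusion.** The point stands in conditional form. As written, the rule makes the standard error of the primary change-score comparison too small by about the missing fraction, and nothing elsewhere in the article corrects this. The false-positive rate exceeds the nominal 5% whenever data are missing: slightly at 5% missing, and more than twofold for two arms and nearly threefold for three groups at 20%. These sizes rest on assumed missing fractions, missingness completely at random, and the mean-change reading of the rule. The direction does not depend on the dropout rate. A separate analysis plan might refine the method, but the sentence in the article does not leave the matter open; it states a rule.

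**What to change.** Delete the fill-in sentence. Replace the intention-to-treat sentence with a statement that all randomised patients are analysed in the group to which they were allocated, using observed data without single imputation. Any of these would serve: a likelihood-based repeated-measures model with baseline as covariate, observed change scores, or proper multiple imputation that carries the imputation uncertainty into the standard error. The choice among them is a matter of preference.

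These methods repair the precision. They do not remove the assumption that patients who are lost behave like completers of their arm; a patient with no value after T0 still adds essentially nothing to the treatment estimate. So add one sensitivity analysis in which patients with a missing T1 time are given no improvement, that is, their T0 time is kept. That value comes from the patient's own data rather than from the other patients in the arm, so it does not recreate the same false precision.

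The cost is a few sentences and a little more analysis work, with no change to visits, recruitment or treatment. Confidence intervals will be visibly wider than under the present rule, by the percentages in the table, because they will reflect the information actually collected.

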#### Presentation of results

The patient recruitment process, the total number of included and excluded patients, as well as the dropout rate will be summarised in a CONSORT flow diagram [84]. All data describing the study population (general profile) will be presented in an overview table. The changes between assessment events and differences between study groups will be displayed in graphs and tables. Significant changes will be marked. Standard deviations and confidence intervals will be used to describe dispersion characteristics.

### Methodology of the qualitative study part

Our exploratory approach applied in the qualitative part evaluates patient's prior experience and usage of MI as well experience they have gained during the study intervention. Current literature did not consider stroke patient's experience obtained with MI. In consequence it is not clear how patients can use MI. As the MI techniques are not yes standardized, no assessment on user experience of MI exists. We have chosen semi-structured interviews to obtain an important insight into patient's experience and attitudes to MI. Additionally, new hypotheses for further investigations can be derived. Embedding MI into physiotherapy is a new therapy approach. The patient's awareness and positive or negative experience during the embedded intervention could be explored in detail during the semi-structured interviews. The qualitative approach allows to discover potentially vital aspects promoting or inhibiting the MI execution. Insight gained from the interviews can help to adapt the MI approach to patient's needs. This may have a critical impact on the further development of MI techniques, in particular, on follow up studies after this pilot trial.

Semi-structured interviews will be conducted twice for this nested qualitative research study. Patients will be interviewed after randomisation to one of the two experimental groups of the RCT and after the last MI intervention session.

#### Sampling and comparison

The inclusion and exclusion criteria of the RCT (please see Table2) describe main characteristics of the patients. For the qualitative part, six to ten patients will be recruited from the whole study sample. Regarding the diversity and heterogeneity of the sample, the following additional criteria will be considered:

- Ability to speak and express thoughts and feelings.

- Inclusion of both genders.

- Inclusion of different ages (younger and older patients).

- Inclusion of patients at different stages of the recovery process (sub-acute or chronic stage).

- Inclusion of patients with different levels of motor impairment.

- Inclusion of different kinds of professions.

- Inclusion of different amount/level of sports before stroke.

- Willingness to participate in the interviews and signed informed consent.

At least three statements of the interviewees will be compared among each other. If possible, a group comparison analysis will be included based on the patient's time since stroke onset.

#### Data collection

After randomisation to one of the experimental groups, patients will be given an additional information sheet and a separate consent form. After receiving informed consent from the participants, data will be collected during semi-structured interviews. The interviews can take place either in the rehabilitation centre or at the patient's home. It is important to create a relaxed and quiet atmosphere. Interviewee and interviewer will sit next to each other on a sofa or chairs close to a table. Interviews will be recorded with a digital voice recorder. The interviewer will take notes during the interview to picture the scenario. These notes will provide the basis for field notes that will be written by the interviewer directly after each interview. Field notes will include information on interview situation; the patient's acting during the interview, her/his facial expressions, gestures, mood, feelings, and course of the interview. Further information about unexpected events or statements, feelings, and impression of the interviewer will be included as well. Depending on fatigue and concentration ability of the patient, interviews will last between 30 minutes up to one hour.

##### Interview guide and questions

The interview can be seen as an active inter-action of two people. Regardless of the prepared interview questions, the interviewer will react on the patient's statements. The interviewer has to formulate spontaneous questions to follow-up answers into more detail.

The interview is divided into three parts: introduction, main and final parts. During the introduction patients will be familiarised with the interview procedure. After starting the recording participants will be asked if she/he has any open questions regarding the information sheet or the informed consent. Additionally, the interviewer will point out that the recording or the whole interview can be stopped at any time if the participant wishes to do so. The introductory part includes broad start questions regarding the stroke event, recovery process, and rehabilitation phase up to this point. Furthermore, interviewees will be asked about previously occurred falls, their fear of falling, and their coping strategies. The participants will be encouraged to talk about their impressions and feelings.

The main part of the interview will focus on the patient's experience with MI. Interviewees will be asked

- what individual experiences they have in learning and using MI,

- what MI means to them,

- what exactly do they imagine,

- when do they use MI,

- why they use MI and

- where do they perform MI.

Additionally, to check for patient's understanding, all participants have to perform and imagine the task 'Standing up from the chair and sitting down'. After performing the task, interviewees will be asked: what they have imagined, how did it feel to imagine, how did they like it, what they think about MI therapy, what they expect from the study intervention, and how MI could help them.

Moreover, time needed for the physical and imagined activity performance will be compared to check for congruence of activity duration. To assess activity duration participants will time physical and imagined activity themselves with a stopwatch. In the last part of the interview the interviewer will briefly summarise patient's statements. Participants will be asked if they would like to make additional comments to anything they have said. Furthermore, interviewees can talk about their impressions from the interview (situation, questions). They can make suggestions, express critique or encouragement. All important statements of patients after stopping recordings will be noted by the interviewer during or after the interview and will be included in field notes.

Semi-structured interviews after the two week intervention period will mainly focus on the experience of patients during this time and, if their usage of MI and their attitude towards MI have changed.

All interview questions were developed based on the findings from Munroe et al. [39] and the interview guide from MacIntyre et al. [38].

#### Transcribing verbal data

All recorded data will be verbatim transcribed by a research assistant with good typewriting skills and with the help of the f4 software for digital transcriptions [85]. As there exists no defined standard to transcribe verbal data, the research assistant will include pauses and repetitions during the interview and will follow the transcription suggestions of Kvale [86] and Bortz [87]. The text will be checked for congruity with the audio data by the research assistant who did the transcription and double-checked by the interviewer. The transcription documents will be complemented by detailed field notes of the interviewer and notes of the analysis process. In combination, these documents will provide a picture of the interview situation and will provide the basis for data analysis.

#### Data analysis

Kvale [86] suggests to start with the analysis already during conduction of interviews. Interviewers should ask 'second questions' during interviews to gain more detailed knowledge about the meanings of patient's statements, e.g. 'Can you tell me more about that?' or 'Could you give me some examples for that?'. Another technique is to condense and summarise statements of the interviewee and check back for correct interpretation directly during the interview. Both techniques will be applied in this qualitative part. Before starting the analysis all documents will be quality checked. To gain an overview on the interviewees and their statements, short case descriptions will be written. These short notes will include descriptive characteristics of the interviewee and main interview topics with suitable quotations. The main analyses of the interview will be done with the Nvivo software [88]. Data collection and data analysis will be based on a phenomenological approach to build a structure from which themes will emerge (thematic analysis). The interview material will be categorized and coded using both, software and personal immersion in the data following Gibbs' recommended approach [89].

#### Quality issues

Transparency of the interview and analysis process is one major opportunity to increase quality in qualitative research and allows a stepwise replication of the research process. Transparency is achieved in this study by documenting 'second questions' during the interviews and maintaining a process for categorisation and coding of transcribed interviews.

An essential approach to increase research quality is to plan and conduct investigations based on trustworthiness, which includes credibility and transferability. Credibility will be addressed in this study by member validation and peer validation [86]. Member validation aims to decrease misinterpretation of interviewees and provides them with the opportunity to comment on the data interpretation. All interviewed participants will be given the opportunity to read the themed analysis to confirm the resource of the themes with their own experiences that have emerged to confirm the validity of the data. Peer examination helps the interviewer to discuss data interpretation with other colleagues and get feedback on the analysis. A third approach to improve quality aspects is the mixed methods design of the research proposal. Quantitative data, e.g. of the KVIQ, can support the qualitative analysis. Triangulation of both methods will provide complementary information and an in-depth understanding of the patient's attitude towards MI and benefits from the intervention study.

#### Presentation of analysis

The analysis will include the common structure of a journal article: introduction/background, methods, results, discussion, and conclusion, adapted to the journal's instructions for authors. Extracts from the transcribed material will be included in the article and will be embedded into quotation marks. The categorisation scheme and the category definitions will be included in the appendix of the publication.

## Discussion

This mixed methods protocol describes an intervention pilot study proposal aiming to compare two different MI techniques in patients after stroke: the sports psychology approach of an embedded MI training into physiotherapy (based on the PETTLEP model) and added MI training after physiotherapy. The third group serves as a control to evaluate the effect of MI vs. A control intervention. A qualitative was integrated into the protocol to gain in-depth knowledge of participant's attitude towards MI and modifications in MI usage during the intervention study.

Findings from fMRI studies provide the neuro-physiological basis of current MI training interventions. Brain areas activated during MI and real movements show a strong congruity for single arm movements as well as complex whole body movements in stroke patients [26,29]. Similar findings were made for other neurological disorders e.g. Mb. Parkinson and amyotrophic lateral sclerosis [90,91]. Intervention studies confirmed a beneficial effect of MI in patients after stroke. Moreover, these results were confirmed in further patient groups, including traumatic brain injury, multiple sclerosis, and Mb. Parkinson [92-94].

The PETTLEP approach was developed for performance improvement of athletes and describes seven important conditions that should be considered during MI training. To this end, the PETTLEP model provides a systematic and embedded approach to MI training. In contrast to PETTLEP, the approach established in stroke rehabilitation adds MI to therapy sessions by including a relaxation phase between physiotherapy and MI training. This added MI training was neither performed in the actual physical training environment nor in the task-specific body position, as is requested for PETTLEP [34]. Based on a preliminary analysis and the current study design we expect that the PETTLEP model can be transferred to stroke rehabilitation.

The perspective that is taken by participants during MI interventions is a controversially discussed issue [34]. Which perspective is the right one? External, hence the participant watching herself/himself or another person performing a task in front of her/his inner eye, or internal, where the participant watching her/his arm or leg from own eye perspective? Do all patients choose the same perspective at the beginning? Does the perspective selection depend on the level of experience with a particular motor task? By determining the learning type and the preferred self-selected perspective the authors hope to contribute towards resolving this debate.

The complex motor task 'Going down, laying on the floor, and getting up again' was chosen for two reasons: firstly, it is clinical important to learn how to get up from the floor, and secondly it is psychologically relevant for all individuals with the risk of falling (fear of falling), in particular for patients after stroke. The study will furthermore provide essential results to determine the benefit of MI as similarly complex motor tasks have not been investigated in stroke rehabilitation before.

Three outcome measures (time and help needed to perform the task as well as level of task completion) will be supplemented by psychological assessment of FOF and motor imagery understanding and ability assessment. Taken together, all assessments will draw a comprehensive picture of a patient's capabilities and subsequent changes during the intervention and follow up period. The motor task assessments will be video recorded. From analysis of assessment videos, it is expected to obtain a more detailed description of the motor task stages, quality of movements, and impact of MI training on the motor task. Furthermore, time ratio of imagination and performance of the motor task will be calculated from patient prediction and actual scores to evaluate the 'Imagination inflation' [47]. These results will provide information about the patient's therapy coherence and acceptance of MI.

Duration of the intervention period was defined after considering MI studies in stroke rehabilitation as well as in sports psychology. In sports psychology, very short MI treatment durations were chosen in comparison to rehabilitation [95]. The duration in this study design is shorter than that of added MI interventions, since the approach using MI embedded in standard physiotherapy requires less time. However, it is expected that the embedding approach will compensate for the reduced duration.

A comparison of embedded and added approaches to MI training in a stroke population sample will contribute to a broader understanding and more focused design of MI interventions in stroke patients. Results will help to answer the question on which MI training approach is more beneficial for patients after stroke and whether a sport psychology model can be transferred directly to rehabilitation practice. Findings from the semi-structured interviews will help to integrate patient's expectations on MI interventions in the design of research studies to improve practical applicability.

